### Home-based resistance exercise (HBRX) intervention

Participants in the HBRX group will be coached, by a qualified study team member, through six phases of the intervention with 2 weeks per phase. Table 1 summarizes the HBRX intervention. Body weight and elastic exercise bands will be used to provide resistance. The lightest resistance band is 3.7 lbs which is low enough for all qualified participants to perform with. Moreover, modifications to exercises are available to accommodate such things as pain. For all exercises, the amputees will wear their prosthetic. A set of commercial elastic resistive bands (TheraBand® CLX) and a stability trainer (Fig. 3; Performance Health, Akron, OH, USA) will be provided to each participant. The use of elastic bands for resistance training can induce results in neuromuscular adaptations and strength similar to those achieved by weight machines and free-weights [23–26].

**Table 1 Tab1:** Home-based resistance exercise intervention

Exercise	Description	Progression of exercise
Plank	Prone lying static position with participant’s weight resting on their forearms while holding their body in a straight line from head to toe. Hold this position, with good form, for as long as possible	Progress to an unstable surface/instability disk
Seated resisted back extension^a^	While seated, place feet into band loops. Have participants pull end loops of the band and create an “X” in front of them. Fold and raise arms to shoulder height. Participants will bend their trunk forward at the waist and return to a “straight back” seated position	Progress to an increased resistance band level
Trunk rotary stabilization^a^	With resistance band anchored at chest level, create tension with band. While standing in line with the band, fully extend arm out to participant’s side at about 30°. Use other hand to push the band forward while maintaining stability in participant’s core. Hold this position for 2–3 s and return to starting position to repeat	Progress to an increased resistance band level
Leg extensions^a^	While standing, place feet into band loops with one seal between them. With feet hip width apart, participants will center their balance onto one leg. Keeping one leg straight, slowly raise and kick backwards without touching the ground. Keep back straight and avoid leaning or bending over. Once finished, place foot back into starting position	Progress to an increased resistance band level
Monster walks^a^	Place legs through band loops making sure they reach right above the knee. Grab the end of the resistance band and while maintaining a slight bend in the knees and hips, take 3 steps laterally while keeping back straight	Progress to an increased resistance band level
Posture reset^a^	Place each hand into CLX™ loop so that hands are one loop apart. Supinate open palms and have participant’s elbows at 90° with hands in front. Extend elbows and shoulder outward and retract shoulder blades	Progress to an increased resistance band level
Abductor resistance^a^	Place feet in the middle two loops of the resistance band. Have the participant grab handles of band and create an “X” behind their knees before pulling the band around the outside of their hips and cross their hands in front of their waist. With a slight bend in the participants’ knees, and maintaining balance, kick one leg out to the side and returning to the starting position. Repeat for opposite leg	Progress to an increased resistance band level
Supermans	While prone lying with arms and legs outstretch, slightly raise both arms and legs off the floor/table in unison	Progress to alternating contralateral arms and legs

^a^Adapted from TheraBand® CLX™ consecutive loops (http://www.therabandclx.com/exercises.html)

**Fig. 3 Fig3:**
[figure not shown]
Elastic resistance band set and stability pad equipment for the home-based resistance

Based on the principles and guidelines of resistance exercise provided by the American College of Sports Medicine (ACSM), the following prescription was crafted [27–30]. Eight exercises will initially be performed 2 days per week for the first phase to familiarize subjects to the exercises and provide instruction on proper form. Exercises were chosen to emphasize core strength [31], dynamic hip and pelvis stability, and lumbar endurance and strength [32]. These exercises include plank, seated resisted back extension, trunk rotary stabilization, leg extensions, monster walks, posture reset, abductor resistance, and prone arm and leg extensions (Supermans) [6]. These exercises were based on our earlier resistance-training programs that improved low back and core strength by training these muscles [33]. For the remaining phases, exercises will be completed three times per week [20]. Participants will be performing three sets of 8–12 repetitions for all exercises, per the ACSM general guidelines for muscular hypertrophy [27–30].

The first exercise session will be performed face-to-face with the participant to allow the investigators to teach the form and make form adjustments. Exercises will be subsequently supervised via Skype® or Facetime with each participant on a weekly basis. Exercise sessions will be documented by the participant in a standard training log. Participant rating of perceived exertion values will be used to assign the band resistance level or number of repetitions for each exercise. The exercises should be perceived as an effort level of between 13 and 14 out of 20 points on the 6–20-point Borg Scale [34], or 6–7 on the Resistance Intensity Scale for Exercise (RISE) scale. The Borg Scale is used for general exercise effort, and the RISE scale was crafted specifically for use with TheraBand® elastic bands [35]. As the participant gets stronger over time, participants will be asked to perform effort levels that fall between 16 and 17 on the Borg Scale and 8 and 9 on the RISE scale. To achieve this, the study team will increase the resistance load/volume (by 2–5%) to keep the effort level at the target during the study [33].

### Wait-list control (CON) condition

Participants who are assigned to the CON group will wait to participate in the resistance training after a 12-week wait period. Participants will follow all instructions provided to them by their physician and care team, but will be asked to refrain from starting any new strengthening exercise protocols or begin any new physical therapies during this time. The participants will be contacted by phone on a monthly basis during the study period to determine if any changes in LBP symptoms, exercise schedule, or medication have occurred.

### Compliance and attrition

Treatment compliance will be assessed by recording the number of completed HBRX training sessions. Participants will be asked to keep an exercise log indicating the exercises performed and RISE and RPE scores for each exercise. Compliance will be defined as completing 85% of all sessions [20]. Members of the study team will be monitoring the exercise performance on a weekly basis. If participants did not remain compliant, their data will not be included in the final analysis. When applicable, participants will be asked for their reasons for poor compliance or dropout. We will collect, assess, and report any spontaneously described adverse events from participants using RedCap data forms. Any unintended or unanticipated adverse events will be reviewed by study physicians for potential medical management. All symptoms will be prospectively followed by phone or in-person until resolution.

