### Pain severity and pain impact on QOL

The primary outcome will be the change in the 11-point NRS_pain_ score during rest and activity from baseline to 3 months. The scale has anchors of 0 (no pain) to 10 (worst imaginable pain). The NRS_pain_ is an accepted outcome measure as described in the Initiative on Methods, Measurement, and Pain Assessment in Clinical Trials (IMMPACT) [38]. Participants will rate their current, worst, and best NRS_pain_ scores over the last 24 h, and the scores will be averaged to create the resting NRS_pain_ value [39]. The participants will also be asked to rate their pain severity during walking [40]. The number, type, scheduled nature of the medication and the medicine dose used to self-manage LBP symptoms will be self-reported by participants at baseline and weeks 4, 8, and 12.

One general QOL instrument and two disease-specific instruments will be used to determine the impact of LBP on participant perceptions of QOL [37]. General QOL will be measured by the Medical Outcomes Short Form-36 (SF-36), consisting of eight domain scores and two component scores (Mental, Physical). The SF-36 instrument has been used to track QOL after traumatic injury such as amputation [41]. Higher scores reflect higher QOL. Low back pain-specific QOL will be measured using the modified version of the Oswestry Disability Index (ODI) [42] and the Roland Morris Disability Questionnaire (RMDQ) [43]. The ODI contains 10 questions about the patient-perceived impact of pain on personal care, walking, lifting, sitting, standing, sleeping, sex life, social life, and traveling. The RMDQ consists of 24 items relating to difficulties with daily activities, house work, stair climb, walking, speed of movements, standing, appetite, and sleep. Both instruments are valid, reliable, reproducible, and sensitive to treatment interventions [42, 43]. Higher scores for both instruments reflect greater pain impact and disability due to pain.

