### Statistical analysis

Statistical analysis will be performed using the Statistical package for the Social Sciences (SPSS v. 24, IBM Corporation, Armonk, NY, USA). An *α* level will be established at 0.05 a priori for all statistical tests. Data will first be examined for normal distribution using the Kolmogorov-Smirnov test, and skewness and kurtosis parameters. Descriptive statistics will be performed to characterize the participants. Means, standard deviation, and frequencies will be obtained for both study groups. The chi-square test for frequency distributions will be used for demographics, and amputation type. Continuous data that are not normally distributed will be transformed prior to analysis.

The main analysis type that will be used to test the hypotheses of aims 1 and 2 will be a mixed-model, repeated measures approach. These analyses will examine the main effects of the exercise treatment on the study outcomes. The independent variables will include study group (HBRX or CON) and time point (baseline, week 12). Dependent variables will include LBP severity, medication use, perceived impact of LBP on QOL (NRS_pain_, medication number, SF-36, ODI, RMDQ) and biomechanical measures (walking velocity, temporal spatial parameters, GRF, key joint angles). Mixed models are the preferred approach to analyze data with repeated measures; these models account for correlation among repeated measurements, flexible time effects, and handle missing data. To test the hypothesis of aim 3, regression analyses will be used to identify significant contributors to the change in pain over 12 weeks. A hierarchical approach will be used to find the model of best fit. Independent variables that will be entered into the models will include changes in lumbar muscle strength, ultrasound measure of lumbar extensor cross-sectional area, and change scores in SF-36, ODI, and RMDQ. In addition to age, sex, and K-classification, models will be adjusted for other participant characteristics if differences are found from baseline to week 12 (Tampa Scale of Kinesiophobia and Pain Catastrophizing Scale scores, daily step number). Subjects who dropped out or missing participant data will not be included in the final analysis, and intention-to-treat will not be utilized. Due to the relatively small study size, actual treatment effects that would be seen may be washed out during an intention-to-treat analysis.

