## Discussion

This study will examine the efficacy of a 12-week HBRX program on LBP severity and pain impact in persons with traumatic unilateral transtibial amputation. Measurements of key physiological and mechanical factors before and after exercise training relative to changes in LBP severity will help improve our understanding of pain responsiveness to exercise. To date, exercise training trials in amputees to treat secondary musculoskeletal system conditions, such as low back pain, are scarce. Physical activity-related intervention studies in amputees primarily focus on the earlier stages of post-amputation care for gait retraining [60] and gait improvement [61, 62]. The use of resistance exercise to help correct secondary musculoskeletal pain conditions is novel, and fills an unmet care need of transtibial amputees for long-term health and well-being.

The HBRX intervention adheres to the exercise prescription principles of the ACSM [30, 63]. A unique aspect of this intervention is that participants will be able to perform the exercise in their home environment, free of travel or financial restrictions that are common barriers to long-term success with exercise engagement. The use of Skype®, Facetime, and other platforms to monitor training will provide the first evidence of the feasibility of such a program in the greater amputee community. If the outcomes occur as hypothesized, this study could generate a working, functional model of resistance exercise for chronic LBP in lower limb amputees that could be quickly implemented in various clinical environments.

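### The 85% session rule can remove only exercise-arm participants from the final analysis, so the primary pain comparison is no longer the randomised one and may be biased, most likely towards HBRX

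*Protocol article*

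**What the plan says.** The Compliance and attrition section of the protocol article gives the measure, "Treatment compliance will be assessed by recording the number of completed HBRX training sessions", the threshold, "Compliance will be defined as completing 85% of all sessions", and the consequence, "If participants did not remain compliant, their data will not be included in the final analysis".

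The Wait-list control (CON) condition section says: "Participants who are assigned to the CON group will wait to participate in the resistance training after a 12-week wait period". The primary outcome is the change in the NRS pain "score during rest and activity from baseline to 3 months", so any training by controls falls after the comparison is complete.

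The Statistical analysis section adds a second exclusion and rules out the usual safeguard: "Subjects who dropped out or missing participant data will not be included in the final analysis, and intention-to-treat will not be utilized". The reason offered is that, in a small trial, "actual treatment effects that would be seen may be washed out during an intention-to-treat analysis". No as-randomised analysis is described, not even as a sensitivity analysis.

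**The concern.** Session completion is observed after randomisation, and only in one arm. Removing participants on it means that the HBRX group analysed is no longer the group that randomisation produced, while the control group is not filtered in the same way.

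Adherence is plausibly related to outcome here. A pain flare or a lack of benefit is a natural reason to miss sessions of a home exercise programme. The Participant characteristics section itself says that kinesiophobia and catastrophizing hinder engagement in exercise and can lower quality of life. People with those traits would tend to be removed from HBRX, while their counterparts stay in CON. A significant difference in pain could then partly reflect who was kept. The deletions also reduce the analysed sample, and the 25% allowance in the Study population section is worded for dropout only.

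**Working it through.** **1. What the threshold means.** The intervention section gives six phases of 2 weeks, with 2 sessions per week in the first phase and 3 per week afterwards.
- Planned sessions: 2 × 2 + 10 × 3 = 34.
- Threshold: 0.85 × 34 = 28.9, so 29 sessions are needed.
- 34 − 29 = 5 sessions may be missed; a sixth removes the participant.
- CON: 0 sessions planned before week 12, so the rule cannot be failed.

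**2. Size of the possible bias.** The protocol gives no adherence figures, so two inputs are assumptions: the fraction f of HBRX removed, and the correlation r between adherence and pain improvement. Blocks of 4 and 40 enrolled imply 20 per arm. With no true effect and a normally distributed outcome, keeping the most adherent 1 − f of HBRX shifts that arm's mean by

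bias (SD units) = r × φ(z_f) / (1 − f).

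For f = 0.25, φ(z_f) = 0.318 and φ(z_f)/(1 − f) = 0.424. That gives 0.127 SD at r = 0.3 and 0.212 SD at r = 0.5. Removing exactly the 5 least adherent of 20 makes the shift slightly smaller. Simulation of that case with a two-sided t test at 0.05 gives:

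| r | Bias in favour of HBRX | Two-sided type I error |
|---|---|---|
| −0.3 | about −0.12 SD | about 6.5% |
| 0 | 0 | about 5% |
| 0.3 | about 0.12 SD | about 6.5% |
| 0.5 | about 0.20 SD | about 9.5% |

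At r = −0.3 the excess false positives favour CON, not HBRX.

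**3. Power.** The stated 16 per group for 80% power cannot be reproduced directly, because no effect size or SD is given. Solving backwards with a two-sided t test at 0.05 (sidedness is not stated) gives a standardised difference of d = 1.02. At that d:
- 16 v 16: 80%, the plan's figure.
- 15 v 15, after the planned 25% dropout from 40 (40 × 0.75 = 30): about 77%.
- 12 v 15, if 3 of the 15 remaining HBRX participants are also removed for non-compliance (an assumption): about 72%.

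In that example the compliance rule accounts for the step from 77% to 72%. The step from 80% to 77% is due to dropout.

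**The case against.** The strongest objection concerns direction and size. A reader might infer that the rule necessarily inflates the exercise effect. The documents do not support that: they report no link between session completion and pain. If adherence is unrelated to outcome, the bias is nil; if people stop because they feel better, it runs against HBRX. Nor do the documents support any particular value of r or f. Extreme choices such as r = 0.7 with 40% removed push type I error to about 23%, but that is an assumed corner and not an estimate for this trial. At moderate values the inflation is modest, and the implied detectable difference is about 1.0 SD. This objection stands as far as certainty and size go.

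A reader might also infer that the rule undermines the Discussion's statement that remote monitoring "will provide the first evidence of the feasibility of such a program in the greater amputee community". That does not follow. Completed sessions are recorded, logs are kept and reasons for poor compliance are sought. Only the outcome analysis excludes these participants; nothing says that adherence data will go unreported.

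The protocol's own defence is that intention-to-treat would dilute the effect in a small trial. Dilution by non-adherence is part of what assigning a home programme achieves. Wishing to see the effect in adherent participants is a reason for a secondary analysis, not for giving up the randomised comparison. Finally, controls can be removed through the separate exclusion for dropout and missing data, so CON is not wholly unfiltered. It remains true that the 85% rule cannot touch that arm.

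**Conclusion.** The point holds. A post-randomisation filter that can act only on HBRX is fixed in the protocol for the final analysis, and no as-randomised analysis offsets it. The loss of the randomised comparison follows from the text alone and needs no assumption about adherence.

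The bias does need assumptions. It most likely favours HBRX, provided that those who miss sessions do worse on pain. For 25% removed and correlations from 0 to 0.5, it ranges from nil to about 0.20 SD, with type I error from 5% to about 9.5%. The added power loss is about 5 percentage points if 3 of 15 HBRX participants are removed after dropout. Because the flaw sits in the primary comparison and is cheap to correct, it should be fixed before the analysis.

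**What to change.** Two passages must change together; removing the compliance sentence alone would leave the second exclusion and the refusal of intention-to-treat in force.

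- **Compliance and attrition:** delete the sentence that excludes non-compliant participants. Keep the 85% definition for description, and report sessions completed.
- **Statistical analysis:** state that the primary analysis includes all randomised participants in their assigned arm, whatever the number of sessions completed, using all available data in the planned mixed model. The section already says that such models handle missing data, which sits badly with deleting participants whose data are missing.
- **Data collection:** obtain week-12 NRS pain from every participant regardless of adherence.
- **Secondary analysis:** retain the 85% compliers only as a labelled per-protocol analysis.

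The cost is protocol wording, one additional analysis and the effort of following up non-adherent participants. No extra patients are needed, and the trial status section reports that recruitment is not complete, so the change is still possible. The downside is that the estimated effect may be smaller than in compliers alone.

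### Adverse events are captured by spontaneous report while contact frequency and prompting differ by arm, so any between-arm comparison of reported harms is open to detection bias

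*Protocol article*

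**What the plan says.** All statements are in the protocol article.

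- **Collection rule** (Compliance and attrition): "We will collect, assess, and report any spontaneously described adverse events from participants using RedCap data forms". The sentence names no arm. The article states no scheduled adverse-event question for either arm.
- **Contact in HBRX** (Home-based resistance exercise intervention): the first session is face-to-face, then "Exercises will be subsequently supervised via Skype® or Facetime with each participant on a weekly basis". Compliance and attrition repeats the weekly schedule: "Members of the study team will be monitoring the exercise performance on a weekly basis".
- **Contact in CON** (Wait-list control condition): "The participants will be contacted by phone on a monthly basis during the study period", with the purpose "to determine if any changes in LBP symptoms, exercise schedule, or medication have occurred".
- **Medication** (Pain severity and pain impact on QOL): use of medicines for back pain "will be self-reported by participants at baseline and weeks 4, 8, and 12". No arm restriction is given, and neither is the mode of collection.
- **After detection** (Compliance and attrition): "All symptoms will be prospectively followed by phone or in-person until resolution".
- **Shared visits** (Primary outcome measures and Table 2): both arms attend at baseline and at weeks 12–13, when there are two post-intervention visits.

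**The concern.** A passive system records an event only if the participant is in touch with staff, still remembers or still has the problem, and chooses to mention it. Here the first condition depends on allocation, because HBRX participants speak to staff about four times as often. Prompting also depends on allocation. CON callers are to ask about back-pain and medication changes, and no equivalent question is stated for the HBRX sessions.

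The article commits to reporting these events. In a two-arm trial they will naturally be set out by arm and compared, whether or not a test is planned. The programme is meant for people with chronic back pain, most of its sessions take place between the weekly video contacts, and the Discussion hopes for quick clinical uptake. A reader will want to know whether the exercise caused harm. Unequal capture blurs that answer and cannot be repaired once the data are in.

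**Working it through.** The article gives no adverse-event rate and no harms comparison, so there is no figure of its own to reproduce. The check asks how far captured events could differ if true event rates were equal.

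**Contacts over 12 weeks.** HBRX: 12/1 = about 12. CON: 12/4 = about 3. Ratio 4:1.

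**Model A: fading recall.** An event falls at random within the interval I between contacts. It is mentioned at the next contact with probability exp(−lag/τ), where τ (weeks) is an assumed recall time. Captured share = (τ/I)(1 − exp(−I/τ)), with I = 1 for HBRX and I = 4 for CON.

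| τ (weeks) | HBRX | CON | Ratio |
|---|---|---|---|
| 1 | 0.63 | 0.25 | 2.58 |
| 2 | 0.79 | 0.43 | 1.82 |
| 4 | 0.88 | 0.63 | 1.40 |
| 8 | 0.94 | 0.79 | 1.19 |
| 26 | 0.98 | 0.93 | 1.06 |

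**Model B: persisting event.** The event stays mentionable and is volunteered with an assumed probability q at each remaining contact. Captured share = average of 1 − (1 − q)^k, with k = 1 to 12 for HBRX and k = 1 to 3 for CON. Because both arms attend two visits at weeks 12–13, the last column adds two contacts to each arm (k + 2 in place of k).

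| q | HBRX | CON | Ratio | Ratio with two shared visits added |
|---|---|---|---|---|
| 0.1 | 0.46 | 0.19 | 2.47 | 0.56/0.34 = 1.65 |
| 0.3 | 0.81 | 0.49 | 1.65 | 0.91/0.75 = 1.21 |
| 0.5 | 0.92 | 0.71 | 1.29 | 0.98/0.93 = 1.06 |
| 0.8 | 0.98 | 0.92 | 1.07 | 1.00 |
| 1.0 | 1.00 | 1.00 | 1.00 | 1.00 |

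**In counts.** Take 20 per arm (40 enrolled; equal allocation inferred from the balanced blocks of 4), an assumed true rate of 30% and τ = 4 weeks. Expected participants with a captured event are 20 × 0.30 × 0.885 = 5.3 in HBRX and 20 × 0.30 × 0.632 = 3.8 in CON. In simulation HBRX showed the higher count in about 65% of trials. Across true rates of 10–50% and τ of 2–8 weeks the figure was 45% to 86%.

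**Prompting.** Both models use the same chance of mention per contact in each arm. For back-pain and medication changes that is not what the article describes, since CON is asked and no such question is stated for HBRX. A higher chance of mention per call in CON would shrink these ratios and could take them below 1. For other events, such as a fall or a sore shoulder, no prompt is stated in either arm, and the models point towards higher capture in HBRX.

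**The case against.** The strongest reply has four parts.

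1. **No planned analysis is affected.** Adverse events are not among the outcomes in Table 2, and the Statistical analysis section plans no harms comparison. This is true, and it limits the weight of the point. But the article does commit to reporting the events, and the bias enters at collection, before any decision on analysis.

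2. **The detail may lie in the full protocol.** Call scripts and form content often do. That would answer a complaint about missing detail. The point here rests on what is stated: a spontaneous-report rule, two different contact schedules, and a prompt given for one arm only.

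3. **The ratios rest on assumptions.** This stands. The article gives no recall time, chance of mention or event rate, and the shared week 12–13 visits narrow the gap, as the last column of Model B shows.

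4. **Some stronger readings fail.** A reader might infer that reported harms must differ between arms purely because of contact frequency. The documents do not support that: with full recall and reporting the ratio is 1.0, contacts differ in content and mode as well as number, exercise may cause real events, and with about 20 per arm chance can hide or reverse the bias. A reader might also infer that back-pain flares in CON will be under-counted. The CON calls ask about precisely such changes, so this does not follow. Nor is the programme unsupervised: it has weekly video supervision, with unobserved sessions in between.

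**Conclusion.** The concern holds as a risk of detection bias. Opportunity to report and prompting both differ by arm under the stated rule, so a difference, or a lack of difference, in reported adverse events could not be read as a difference in harm.

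The size is unknown. With equal true rates and the same chance of mention per contact in each arm, the assumed models give a capture ratio (HBRX to CON) from about 1.0 to about 2.6, and nearer 1 when recall is long or the shared final visits pick up missed events. For events that neither arm is asked about, the likely direction is over-representation in HBRX. For back-pain worsening the direction is uncertain. The pain outcome and its planned analysis are not touched by this point. The change is worth making because it costs little and cannot be made afterwards.

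**What to change.** Replace the spontaneous-report rule with matched, prompted collection at contacts that already exist:

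- Ask one short, non-leading adverse-event question in the same words in both arms at three matched times: the weekly HBRX session and the monthly CON call nearest week 4, the same pair nearest week 8, and the week 12–13 visit.
- At those contacts, ask about change in low back pain in the same words in both arms.
- Record the source of each report on the REDCap form: scheduled question, volunteered at another contact, or other.
- Base the between-arm harms table on the matched contacts only, and list events volunteered at other times separately by arm.

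The cost is two brief questions at three existing contacts and one form field. Contacts become slightly longer, and the total event count will rise because prompted collection finds more. Treatment, sample size and the primary analysis are unchanged. For participants already followed under the old rule, report their events separately and state the rule that applied.
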